### Power calculations

The following power calculations are based on effect sizes and CIs observed in our previously published results, which used data from 110 000 individuals prescribed either varenicline or nicotine replacement therapy.^13^ Based on the rate of 18 000 new prescriptions per year observed in the CPRD from 2006 to 2011,^13^ we estimate that with a further 4 years of follow-up the number of patients prescribed either varenicline or nicotine replacement therapy will have increased by 72 000. Therefore the total expected sample size for analysis will be around 180 000.

In our previous analysis using CPRD data the age-adjusted and sex-adjusted HR for self-harm/suicide for varenicline versus nicotine replacement therapy at 9 months was 0.73 (95% CI 0.54 to 0.99); after adjusting for possible confounders this became 0.90 (95% CI: 0.66 to 1.22).^13^ A 70% increase in sample size would lead to a reduction of the SE by a factor of 1.3, reducing the breadth of the above CI in the adjusted analysis from 0.56 to 0.43.

Rare outcomes, such as self-harm and suicide were used in previous analyses; in this project we will have greater power to explore more common outcome measures. For example, in the previous analysis the 9-month age-adjusted and sex-adjusted HR for all-cause mortality 9 months after first prescription for varenicline versus nicotine replacement therapy was 0.43 (95% CI 0.35 to 0.53); after controlling for possible confounders this became 0.49 (95% CI 0.40 to 0.61). A 70% increase in sample size would lead to a reduction of the SE by a factor of 1.3, reducing the breadth of the above CI in the adjusted analysis from 0.21 to 0.16.

For the effects of varenicline versus nicotine replacement therapy on all-cause mortality, instrumental variable analysis found a risk difference of 0.7 (95% CI −3.3 to 4.7) per 1000 patients treated after 9 months. We estimate that a 70% increase in sample size would narrow the CIs from 8.0 to 6.2.

Using data from our previous project, within 2 years of first prescription, we found 2517 admissions for respiratory disease among 1374 patients; 3144 admissions for cardiovascular disease among 1022 patients; and 3277 admissions for depression or anxiety among 213 patients. This is more events than we found for suicide and self-harm in our previous study; therefore we believe that there will be enough events for this analysis.

To investigate differences in healthcare-seeking behaviour of smokers by SEP we will combine the sample used for the health outcomes described above with a sample of all other patients indicated as a current smoker after the 1 September 2006.

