### Inclusion and exclusion criteria

We will include patients who were older than 18 and were prescribed medicines in British National Formulary (BNF) category 4.10.2 (Nicotine Dependence) from 1 September 2006, when varenicline was introduced to the UK, to the present. We will use patients prescribed other smoking cessation products (nicotine patches, gum, lozenges, and inhalers) as controls for patients prescribed varenicline. We will include patients whose records were classified as ‘acceptable’ by the CPRD from all ‘up to standard’ general practices (GPs) at least 18 months prior to date of entry of each cohort (1st March 2005). Up to standard GPs are practices that have submitted data that meets the CPRD quality control thresholds. Patient data are defined as ‘acceptable’ by the CPRD if they meet minimum quality control standards, for example their registration period with their GP is valid.

We will exclude patients who registered at a GP less than 365 days before the first recorded prescription, to allow for high-quality assessment of baseline data and possible confounders. Patients prescribed bupropion in the year before their index prescription of varenicline or nicotine replacement therapy will be excluded from the analysis. In the primary analysis we will exclude patients initially prescribed nicotine replacement therapies and varenicline together, although in our previous analysis this only occurred for 0.25% of all prescriptions.^13^

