#### Analysis 1: Conventional cox regression

In our first analysis, a conventional observational analysis, we will estimate HRs of the outcomes using Cox-proportional hazards models and the actual prescriptions issued to the patients.^29^ Each patient's date of entry into the cohort will be the date they were first prescribed a smoking cessation therapy. The date of exit for each outcome will be the date on which they first have an event, or are censored due to end of follow-up or death or leaving the practice. We will report these associations adjusted for basic confounders (age and gender), and results adjusted for all measured covariates described above.

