### Socioeconomic variation in effectiveness of smoking cessation treatments

This project will use the entire sample of patients indicated as a smoker at any point after 1 September 2006. We will assign a measure of area level deprivation to each patient using their home address postcode and to each GP using the GP postcode. Deprivation levels will be based on the Indices of Multiple Deprivation (IMD), which are available from the ONS and are updated every 2 years. We will use the most recent IMD statistics preceding the date of entry into the study for each patient. Although area level deprivation statistics will only be a proxy for individual level deprivation, these demonstrate the expected associations with smoking prevalence.^41^ We will investigate whether the proportion of smokers who attend their GP for smoking cessation treatment differs by IMD, and whether there are any differences in prescribing of varenicline versus nicotine replacement products between areas of high and low deprivation.

By using individual and GP level IMD codes, we will investigate whether the effects of smoking cessation therapies differ by IMD at the level of GPs and at the individual level. We will investigate treatment compliance by reporting the total number of prescriptions issued after the initial prescription. We will estimate the effects of smoking cessation therapies within subgroups defined by IMD level at the individual and GP level using the three methods described above, multivariable-adjusted Cox regression, propensity score regression and instrumental variable analysis.^29^
^32^
^42^ The cohort of patients will be defined as described above. We will report these associations adjusted for basic confounders (age and gender), and results adjusted for all measured covariates described above. Analyses will account for clustering of patients by GPs.

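### The uptake-by-deprivation comparison joins a treated sample cut by prescription-based rules to all other smokers, who have no matching registration rule or entry date

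*Protocol article*

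**What the plan says.** All references are to the Protocol article.

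- **Sample for the uptake question.** The end of Power calculations says "we will combine the sample used for the health outcomes described above with a sample of all other patients indicated as a current smoker" after 1 September 2006. The section on socioeconomic variation says: "This project will use the entire sample of patients indicated as a smoker at any point after 1 September 2006".
- **Question asked of that sample.** The same section says: "We will investigate whether the proportion of smokers who attend their GP for smoking cessation treatment differs by IMD". A second comparison there concerns "whether there are any differences in prescribing of varenicline versus nicotine replacement products between areas of high and low deprivation".
- **Rules already applied to the treated part.** Inclusion and exclusion criteria says: "We will exclude patients who registered at a GP less than 365 days before the first recorded prescription". It also says: "Patients prescribed bupropion in the year before their index prescription of varenicline or nicotine replacement therapy will be excluded from the analysis". Patients started on varenicline and nicotine replacement together are left out of the primary analysis. Exposure measures adds that there must be no related product in the 12 months before the index prescription.
- **Entry and IMD.** In Analysis 1, each patient's "date of entry into the cohort will be the date they were first prescribed a smoking cessation therapy". The IMD rule is: "We will use the most recent IMD statistics preceding the date of entry into the study for each patient".

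**The concern.** A proportion treated needs its numerator and denominator drawn under the same rules and watched for comparable time. Here the treated part is what remains after several rules tied to a first prescription, and the rest is the complement of that sample among current smokers. A smoker prescribed nicotine replacement five months after registering fails the 365-day rule. That smoker is not in the health-outcomes sample and so, read literally, is among the others. A smoker who only ever received bupropion is there too, because the study exposures are varenicline and nicotine replacement.

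The other smokers also have no stated starting point. The only entry date the article defines is the date of a prescription, which an untreated smoker does not have, yet the IMD rule needs an entry date for each patient.

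What is at stake is the statement about inequality in access to treatment. If short registration or frequent moves are commoner in one deprivation group, uptake there could look lower with no true difference in treatment.

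**Working it through.** **1. The plan's own figure.** The expected treated sample is 110 000 + 4 × 18 000 = 182 000, which agrees with the stated figure of around 180 000. It does not bear on this point. No size, precision or treated proportion is stated for the wider smoker sample.

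**2. The rules side by side.**

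| Rule | Treated part | Other current smokers |
|---|---|---|
| Age over 18 | stated | not restated |
| Acceptable record, up-to-standard practice | stated | worded generally, may apply |
| 365 days registered | before first prescription | cannot apply as written: no prescription |
| No related product in prior 12 months | before index prescription | no counterpart |
| No bupropion in prior year | before index prescription | no counterpart |
| No joint start | primary analysis | no counterpart |
| Entry date | first prescription | none stated |

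**3. Effect on the proportion treated.** Let p be the true share of smokers treated and f the share of treated smokers who fail the rules. The documents give neither, so both are assumed.

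- Ineligible treated smokers counted as untreated: observed share = p(1 − f).
- Ineligible treated smokers dropped altogether: observed share = p(1 − f) / (1 − pf).
- Any prescription flagged as treatment: observed share = p.

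Example with p = 30% in both groups, and f = 5% in the least and 10% in the most deprived:

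- Counted as untreated: 0.30 × 0.95 = 28.5% and 0.30 × 0.90 = 27.0%, a false gap of 1.5 points and a ratio of 27.0/28.5 = 0.947.
- Dropped: 0.285/0.985 = 28.9% and 0.270/0.970 = 27.8%, a ratio of 0.962.

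With f = 5% and 20%, counting as untreated gives 28.5% and 0.30 × 0.80 = 24.0%, a gap of 4.5 points.

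The table gives the ratio of observed uptake, most to least deprived, when the true ratio is 1.00:

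| Assumed f, least v most deprived | Counted as untreated | Dropped (p from 10% to 30%) |
|---|---|---|
| 10% v 10% | 1.000 | 1.000 |
| 5% v 10% | 0.947 | 0.952 to 0.962 |
| 10% v 20% | 0.889 | 0.898 to 0.917 |
| 10% v 30% | 0.778 | 0.794 to 0.829 |

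The first row matters. With equal f the level falls (p = 20% becomes 0.20 × 0.90 = 18% if counted as untreated), but the ratio does not move. If the least deprived group had the higher f, the ratio would exceed 1.

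**4. Which rules could carry weight.** Joint starts were 0.25% of prescriptions in the earlier analysis. As a rough guide that is a factor of 1 − 0.0025 = 0.9975, which is negligible. The Introduction calls bupropion rarely prescribed. That leaves the registration and prior-use rules, for which no figure is given.

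**5. Observation time.** This part remains even if every prescription is flagged. At a constant treatment rate λ, the share ever treated after time T is 1 − exp(−λT), which rises with T. A smoker observed for a few months counts the same in a crude proportion as one observed for years. Two deprivation groups with the same λ but different lengths of registration would show different proportions.

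**The case against.** The strongest reply is that the article never says treated means belonging to the health-outcomes sample. The uptake question is put in terms of smokers attending for treatment. Exposure measures says the therapy file lists all prescriptions issued, so anyone with a prescription could be flagged whatever their eligibility. Joining the existing cohort to all remaining smokers may simply be a way of describing the full smoker population. That stands: a reader might infer that ineligible treated smokers will be coded untreated, but the document does not say so.

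It also stands that the other smokers cannot be said to face no rules. The data-quality rule is worded generally, and the socioeconomic section says the cohort is defined as described above. That sentence, however, follows the one on treatment effects within IMD subgroups. The 365-day rule is counted back from a prescription, so it cannot carry over to people without one.

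A third reply is that the entry date in Analysis 1 belongs to the Cox models, and that a condensed article may leave an index date for a descriptive comparison to the full protocol. As a bare omission that would be fair. But the article does fix how the sample is assembled and which date the IMD rule uses, and the two do not fit together for untreated smokers. Correct flagging would not cure the unequal observation time.

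**Conclusion.** The point holds for one comparison: the proportion of smokers treated, by IMD. Its two parts are assembled under different rules, and the untreated part has no workable entry date. If prescribed-but-ineligible smokers are classed as untreated or dropped, uptake is understated. The IMD gradient may also be biased, but only if ineligibility or observation time varies with deprivation. That is plausible for recent registration, but the documents do not quantify it. The ratios of 0.78 to 0.96 above therefore rest wholly on assumed inputs with unequal failure fractions and show possible size only.

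A reader might go further and conclude that the gradient is biased, or that the whole deprivation study is compromised. The documents support neither. Equal ineligibility and equal observation time across IMD groups would leave the ratio unchanged. The comparison of varenicline with nicotine replacement prescribing and the treatment effects within IMD subgroups do not use the untreated smokers and are not affected.

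**What to change.** For the uptake question only:

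- Define one smoker cohort with the same age, data-quality and registration rules for everyone, and a common index date. One choice is the first current-smoker record on or after 1 September 2006 while the patient is registered.
- Assign IMD at that date.
- Count any cessation prescription from the index date as treated, including those that fail the rules for the treatment-effect cohort.
- Compare uptake within a fixed window, or as a rate per person-year.
- If a 365-day registration rule is kept, apply it to all smokers. Then either exclude those already treated before entry or count their earlier prescription. Starting the clock at one year and counting only later prescriptions would put smokers treated in their first year back among the untreated.

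Keep the existing exclusions for the treatment-effect analyses. The cost is protocol wording and one more cohort derivation from CPRD records. If a minimum registration period is kept, some recently registered smokers are lost.

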### Data collection and linkage

We will use linked Hospital Episodes Statistics (HES) and ONS mortality data to define frequency of GP and hospital attendance, frequency of all-cause and cause-specific hospitalisation and all-cause and cause-specific mortality. We will test these hypotheses using data from GP practices linked to external data sets only.

These are important hard outcomes for our study. We have already established that for certain outcomes, such as cause specific mortality the linked ONS data are more accurate.^18^ While it is possible to investigate these outcomes using CPRD data from GPs, the data are less precise and consistently recorded.^18^ Thus analyses using linked data are likely to be more precise. Furthermore, the linked data provide direct evidence about secondary care attendance of patients via the HES data. Again, while there are some data about referrals to secondary care in the main tables of the CPRD, the data are not as comprehensive as HES data. Our outcomes of interest occur after September 2006; therefore, we believe that the linked HES and ONS data will provide sufficient coverage for these outcomes.

### Data analysis

#### Exposure measures

First time users of the smoking cessation therapies (varenicline or nicotine replacement therapy) will be defined as people who received at least one prescription of the product after the 1 September 2006 but with no use of a related product during the 12 months before the index date (the first date on which a prescription was issued). Langley *et al*^19^ found the smoking cessation prescription data in the THIN database, which is closely related to the CPRD, to be highly comparable to national dispensing data. The prescriptions will be defined by the therapy file in the CPRD, which contains a list of all prescriptions issued to patients by their GP. Each therapy record records the date a prescription was issued, the quantity of drug prescribed and the dose.

The primary analysis will be limited to the first treatment episode. This is analogous to an intention-to-treat analysis in a RCT.^20^ This ensures that the target parameter estimated in the observational study will be comparable to the parameter estimated by a RCT. For example, if patients’ treatment adherence and duration is related to whether they experience adverse events, then definitions of exposure which are based on treatment adherence may provide unreliable evidence of the causal effect of the prescription on adverse outcomes. This analysis framework was described in Hernán *et al* (2008). The intuition is that most randomised trials recruit individuals and then split participants into different treatment arms. This means that comparison groups are implicitly from first treatment. The primary analysis in an RCT typically reports an intention to treat estimate, which is the difference in allocation between arms of the trial based on allocation, rather than the treatment the participant received. To obtain results that are comparable to a randomised trial Hernán argued that analysts need to construct cohorts that also follow-up patients from first treatment, rather using retrospectively defined exposures (eg, retrospectively defining exposure as ever exposed to varenicline).

To mimic an intention-to-treat analysis in an RCT, in our primary analysis patients who are initially prescribed nicotine replacement therapy, but later switch to varenicline, will be allocated to nicotine replacement therapy and vice-versa. We will use an intention-to-treat design for two reasons. First, while there are theoretical statistical models for estimating the effects of treatment switching such as marginal structural models, these methods require the strong assumption that there are no unmeasured confounders and typically require detailed data on time-varying confounders, which are unlikely to be available in the CPRD. Second, to our knowledge there are no instrumental variable methods to estimate the effects of switching treatment. However, we will investigate the number of participants who switch treatment as a sensitivity analysis.

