#### Confounding factors

We will include gender, age in years at time of first prescription, previous psychiatric illness/consultation, previous use of psychotropic medications such as hypnotics, antipsychotics and antidepressants, previous self-harm, measures of alcohol consumption where appropriate mean/median number of GP visits per year, body mass index, SEP (deprivation score for area or residence) and major chronic illness (including: diabetes, cancer, arthritis) using the Charlson index.^26^
^27^ Relevant Read codes will be identified either by validated code lists or by searching for each of these events in the Read code dictionaries to identify any missing Read codes. Collider bias is a potential threat to the analysis; this type of bias occurs when the association between two variables changes on conditioning of a third variable if the third variable is affected by the first two variables. Collider bias could occur if we conditioned on events that happened as a result of the prescription the patient was issued. To prevent this bias from affecting our results, we will define each covariate using data inputted prior to the first prescription.^28^ If there are missing data in the covariates we will consider using multiple imputation.

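### The 12-month washout can admit patients with older prescribed cessation treatment as first-time users, and no listed covariate records that history, so the Cox and propensity score analyses may keep residual confounding, chiefly for abstinence

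*Protocol article*

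**What the plan says.** All references are to the protocol article.

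- **Exposure measures.** The cohort is introduced with "First time users of the smoking cessation therapies (varenicline or nicotine replacement therapy) will be defined as people who received at least one prescription". That prescription must fall after 1 September 2006, and the washout condition reads "but with no use of a related product during the 12 months before the index date". The index date is "the first date on which a prescription was issued". The primary analysis is limited to the first treatment episode. The therapy file is described as listing all prescriptions issued by the GP.
- **Inclusion and exclusion criteria.** Prescriptions count "from 1 September 2006, when varenicline was introduced to the UK, to the present". The registration rule is also one year: "We will exclude patients who registered at a GP less than 365 days before the first recorded prescription". So is the bupropion rule: "Patients prescribed bupropion in the year before their index prescription of varenicline or nicotine replacement therapy will be excluded from the analysis".
- **Confounding factors.** The list opens "We will include gender, age in years at time of first prescription, previous psychiatric illness/consultation". It goes on to psychotropic medication, self-harm, alcohol, GP visits, body mass index, area deprivation and chronic illness by the Charlson index. It names no earlier nicotine replacement, varenicline or bupropion prescription and no earlier quit attempt. All covariates are to be defined from data entered before the first prescription.
- **Analyses 1 and 2.** The fully adjusted Cox model and the propensity score both use this list.
- **Analysis 3.** The instrumental variable analysis uses the physician's seven prior prescriptions as a proxy for prescribing preference.

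**The concern.** A 12-month washout is a common choice and no error in itself. The difficulty is the combination: the cohort is called first-time users, the look-back stops at one year, and the adjustment set does not record what happened before that year.

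A patient who tried prescribed nicotine replacement in early 2005 and was next prescribed a product in October 2006 passes the rule. If that product is varenicline, the patient is a first-time user of varenicline; if it is nicotine replacement, a first-time user of nicotine replacement.

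An earlier attempt that failed plausibly influences which product is chosen next and also plausibly predicts relapse. If both hold, it confounds the abstinence comparison (Outcome 1), and neither the Cox adjustment nor the matching removes it. The bias would not shrink as the sample grows, which matters in a study that expects to detect fairly small effects.

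**Working it through.** **1. Who can pass the rule.** If the index date meant the first prescription ever in the record, the 12-month clause would have no function. The natural reading is the first prescription after 1 September 2006. Then:

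- Nicotine replacement in early 2005, varenicline in October 2006: passes, enters as varenicline.
- Nicotine replacement in 2008, varenicline in 2010: indexed in 2008, stays in the nicotine replacement arm.
- Bupropion more than a year before index: passes, because the exclusion covers one year only. Bupropion does not set the index date, so this is not strictly confined to the period before September 2006. The Introduction describes bupropion as rarely prescribed.
- Earlier varenicline: not possible on this reading, since varenicline reached the UK on 1 September 2006.

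The group is therefore bounded: mainly nicotine replacement or bupropion before 1 September 2006 and more than 12 months before index.

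**2. Whether another item captures it.** The nearest covariate is previous psychotropic medication, illustrated by hypnotics, antipsychotics and antidepressants. That does not cover nicotine replacement.

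**3. Possible size.** The article gives no share of earlier users by arm and no relapse ratio for them, so every input here is an assumption. Let p1 be the share of earlier users in the varenicline arm, p0 the share in the nicotine replacement arm, and RR their relapse ratio relative to other patients. The factor by which the varenicline versus nicotine replacement ratio is multiplied is

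F = [1 + p1(RR − 1)] / [1 + p0(RR − 1)].

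| p1 v p0 | RR = 1.1 | RR = 1.5 |
|---|---|---|
| 30% v 30% | 1.03/1.03 = 1.00 | 1.15/1.15 = 1.00 |
| 30% v 20% | 1.03/1.02 = 1.01 | 1.15/1.10 = 1.05 |
| 40% v 20% | 1.04/1.02 = 1.02 | 1.20/1.10 = 1.09 |
| 50% v 20% | 1.05/1.02 = 1.03 | 1.25/1.10 = 1.14 |
| 20% v 30% | 1.02/1.03 = 0.99 | 1.10/1.15 = 0.96 |

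Since F − 1 = (p1 − p0)(RR − 1) / [1 + p0(RR − 1)], the bias vanishes if the arms are balanced and reverses if the imbalance does.

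**4. Scale against sampling error.** The stated sample size reproduces: 110 000 + 4 × 18 000 = 182 000, against around 180 000. The article reports that 74% of patients had a later smoking record and that 66% of these were current smokers. That gives 0.74 × 180 000 = 133 200 patients. With an assumed equal split (66 600 per arm), the 95% half-width of a risk difference is 1.96 × √(2 × 0.66 × 0.34 / 66 600) = 0.0051, about 0.5 percentage points before clustering. A factor of 1.02 on 66% is 0.66 × 0.02 = 0.013, or 1.3 points. A modest imbalance, if present, could therefore exceed sampling error.

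**The case against.** **Mixing is not confounding.** Earlier users in both arms bias the comparison only if their share differs by arm and their history predicts the outcome. The article shows neither. A reader might infer an imbalance from the dates, since early entrants could have used nicotine replacement before but not varenicline. The dates show only that earlier treatment was not varenicline; they do not show that earlier users went disproportionately to varenicline. This objection stands. A claim that confounding is demonstrated, or that varenicline's effect on abstinence is understated, is not supported.

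**The group is limited.** With the index at the first prescription after 1 September 2006, the share of earlier users plausibly falls as accrual continues. This also stands, and the larger shares in the table may be too high for the whole cohort.

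**Other outcomes are less exposed.** Even a factor of 1.09 would move the earlier adjusted mortality hazard ratio of 0.49 only to 0.49/1.09 = 0.45 or 0.49 × 1.09 = 0.53, inside its interval of 0.40 to 0.61. Hence the restriction to chiefly abstinence.

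**Comparability with a trial.** A reader might take "This means that comparison groups are implicitly from first treatment" as a claim that patients are treatment-naive, and conclude that comparability with a trial fails. That sentence describes randomised trials, and the contrast drawn is with exposure defined retrospectively. It concerns starting follow-up at initiation, which the design does. The stronger conclusion does not follow.

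**Unobserved confounding is acknowledged and a third method is planned.** This is partly an answer. The instrumental variable analysis does not rest on measured covariates alone. But earlier GP prescriptions are recorded where the look-back reaches, so a general caveat about unobserved confounders does not justify leaving them out of the other two analyses.

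**Conclusion.** The point holds as a gap in definition and adjustment, not as a demonstrated bias. The text establishes that the one-year look-back can admit patients with older prescribed cessation treatment under a first-time label, and that the covariates feeding analyses 1 and 2 do not record it. Residual confounding in those two analyses is therefore possible, chiefly for abstinence.

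Under the assumed shares and relapse ratios the bias factor runs from about 0.96 to 1.14, and is 1.00 with balanced arms. Neither size nor direction can be fixed from the article. The bounded group rests on reading the index date as the first prescription after 1 September 2006. Analysis 3 is affected only if earlier treatment is associated with the physician's previous prescriptions. The change is worth making because it is inexpensive and uses data the study already holds.

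**What to change.** 1. Add to the covariates in Confounding factors, and so to the propensity score, an indicator of any earlier cessation prescription by product, together with length of prior record. These pre-date the index prescription, so they respect the article's own rule against conditioning on later events.
2. Report earlier treatment by arm and by level of the instrument. The first shows whether an imbalance exists; the second whether the instrumental variable analysis is exposed to it.
3. Repeat the main contrasts in patients with no earlier cessation prescription on record.
4. Call the cohort new users after a 12-month washout, and state which prescription sets the index date.

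**Cost.** A wording change, a few derived variables from the therapy file and one sensitivity analysis. Look-back length varies between patients, with only 365 days of registration guaranteed. Treatment obtained outside GP prescribing stays unmeasured, so even the restricted group cannot be called treatment-naive. The restricted analysis has fewer patients and is less precise.
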